#### Secondary Outcome Measures

The severity of participants’ social anxiety will be assessed with a self-report version of the Liebowitz Social Anxiety Scale (LSAS-SR) [46,47]. Assessment with the LSAS-SR will take place at preintervention, postintervention at week 1, after finishing the online program at week 5, and during follow-ups at 3 and 12 months. A change in score from baseline will be assessed. The LSAS-SR is a 24-item scale that measures fear or anxiety and avoidance of different social situations over the past week. It consists of 11 items addressing social interaction situations (eg, “meeting strangers”) and 13 items addressing public performance situations (eg, “acting, performing, or giving a talk in front of an audience”). Each item is rated twice using 4-point Likert scales, one for the intensity of anxiety ranging from 0 “none” to 3 “severe” and the other one for the frequency of avoidance of the situation ranging from 0 “never” to 3 “usually.” An overall score is calculated by summing the anxiety and avoidance ratings for all 24 items, with results ranging between 0 and 144. LSAS-SR also allows the calculation of anxiety and avoidance subscales, where each can be divided into 2 subscores: social interaction anxiety and performance anxiety within the anxiety subscale, and social interaction avoidance and performance avoidance within the performance subscale. A higher score indicates more severe symptoms. To assess the eligibility of the Lithuanian version of LSAS-SR, a pilot study was conducted with 168 participants aged 18‐25 (mean age 21.01, SD 2.67) years. The scale showed good internal consistency (α=.92 to .95) and sufficient construct validity (RMSEA=0.06) and is suitable for use in the young adult sample.

Individuals’ level of apprehension regarding the possibility of receiving negative evaluations will be assessed using a self-report questionnaire, the Brief Fear of Negative Evaluation Scale (BFNE) [48]. Participants will be instructed to complete the questionnaire preintervention, postintervention at week 1, after finishing the online program at week 5, and during follow-ups at 3 and 12 months. The BFNE is a 12-item, 5-point Likert-type scale, ranging from 0 “not at all” to 4 “extremely.” The statements in the scale describe the presence or absence of fear or worrying about being negatively regarded by others (eg, “I am frequently afraid of other people noticing my shortcomings”). Individuals who score high on the BFNE exhibit a heightened fear of negative evaluations, a characteristic associated with social anxiety. To circumvent the prospects of being unfavorably judged, individuals with high scores tend to adjust their behavior accordingly [48,49]. The study will use a validated Lithuanian version of the BFNE. According to a previous study [50], the internal consistency of this version is satisfactory (α=.85). Additionally, a previously mentioned pilot study also included the Lithuanian version of the BFNE, revealing good internal consistency (α=.94) and adequate construct validity (RMSEA=0.04).

#### Other Outcome Measures

##### In-Session Assessments

A series of single-item measures will take place before and after the speaking tasks, as well as following the review of the audio recording. Each measure will be rated on a scale from 0 to 100, but using different verbal anchors at the extremes. The subjective level of distress (using the Subjective Units of Distress Scale [SUDS]), rated from “no distress” to “extremely high distress,” will be measured once the speaking task is presented to the participant and twice after the task is completed, asking the participant to indicate the SUDS after the task and the highest level reached during the task. Participants will also be asked to indicate their negative beliefs and expectations related to the task; that is, they will be asked to provide a qualitative description of their fears and concerns related to upcoming task performance, and then they will also be asked to rate the likelihood of these fears and concerns to become true from “definitely not going to happen” to “definitely going to happen,” and after the task was completed and the audio recording was reviewed, participants will once again rate to which extent their expectation has proven to be true from “not true at all” to “completely came true.” Furthermore, participants will be asked to rate the quality of their performance from “completely failed” to “completely succeeded” right after each task and following the review of the audio recording.

The sense of presence will be measured in two different ways. First, after each task, using a scale from 0 “definitely not” to 100 “definitely yes,” participants will be asked to rate whether they actually had the sense of “being there” while performing the speaking task in VR. Second, to assess the overall experience, the sense of presence of participants will be measured with the Igroup Presence Questionnaire (IPQ) [51]. Assessments will be taken after a 1-session VR exposure treatment in the 1-session condition or after each session in the 3-session exposure condition, and participants will be asked to answer questions about their sense of presence during the whole session. This questionnaire consists of 14 items measuring 3 subscales: spatial presence, involvement, and experienced realism. Each item is rated on a 7-point Likert scale, and the score is calculated by summing the ratings for each item. The scale previously showed good psychometric properties (α=.87) [52].

At the end of the 1-session format or before closing the last of the 3-session format, participants will be asked to evaluate the format of the intervention they participated in. Using a 7-point semantic differential type scale, the participants will be asked to rate their attitude and experience regarding 5 characteristics: convenience, duration, fatigue, intensity, and adaptability. The two groups will receive slightly different and specific parallel wording in the instructions. For the 3-session format, “You met the researcher three times and each session took about an hour, how would you rate that format?” while for the 1-session format, “You met the researcher one time and this session took about three hours, how would you rate that format?”

##### Other Measures

The PHQ-9 [53] will only be used for screening purposes during the participant selection stage and will serve as one of the exclusion criteria. PHQ-9 is a short but reliable tool to assess the severity of depressive symptoms. PHQ-9 consists of 9 items that are rated depending on how often the symptoms were bothersome using a 4-point scale, ranging from 0 “not at all” to 3 “nearly every day.” The ratings are summed for the total score, and a score of 15 and above indicates a risk of severe depression [54]. The Lithuanian version of the PHQ-9 has been validated and showed good psychometric properties (α=.86) in a young adult sample [55].

Treatment satisfaction and negative effects will be assessed posttreatment after finishing the online program at week 5. Participants will be asked to answer questions about treatment (both VR exposure sessions and online program) satisfaction and report negative effects as well as rate the level of these effects. Treatment engagement will be measured by the number of modules opened and will be analyzed descriptively. Treatment expectancy will also be measured and used for secondary data analysis.

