**Methods:**

This randomized controlled trial will aim to recruit 86 higher education students experiencing high levels of public speaking anxiety, who will be randomized into one of two conditions: either 1 or 3 sessions of VR exposure therapy, with the same total number of exposure exercises. Both conditions will be followed by the same 4-week online program to encourage in vivo exposure tasks for both conditions. The study will be an exploratory superiority trial testing whether one of the conditions is superior to the other. The primary outcome will be the Public Speaking Anxiety Scale. Assessments will take place pretreatment, at the beginning of the face-to-face session, during the face-to-face session, 1 week after the last VR exposure session, at the end of 4 weeks of the online program, and at two follow-ups at 3 and 12 months after finishing the online program, or equivalent time if the online program was discontinued. Repeated measures within-between ANOVA, the reliable change index (RCI), and effect sizes will be used as statistical analyses, and intention-to-treat will be the primary analysis approach; additional per-protocol analysis will be reported.

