VR exposure introduces an additional dimension to the debate between prolonged and spaced exposure approaches. In VR research, the concept of presence is understood as the extent to which a person connects and engages with the virtual environment [33] or the interpretation of the virtual environment as if it were real [34]. It has been suggested that a sense of presence in a VR environment is necessary for exposure success, as virtual stimuli need to be perceived as real enough to activate the fear system [35]. It might be that presence in a VR environment during exposure might diminish if fear-evoking tasks are performed repeatedly in a short period of time in a single long session. For example, an observed reduction in anxiety might be due to a reduction in presence, but not due to habituation or new safety-representing associations. Factors influencing presence in a VR environment are not widely studied, and the effect of duration in a VR environment on the sense of presence is not clear [36-38]. Research also shows a practical problem of longer VR sessions being associated with increased motion sickness risk [36,39]. This has been found to be associated with increased reaction times and increased heart rate [40], which might negatively impact exposure task effectiveness.

The most commonly mentioned advantage of 1-session treatment is that it offers a clear benefit of saving cost, time, and resources [32]. And of course, for research purposes, the 1-session treatment intervention strategy greatly reduces the issue of participant retention. However, in a traditional therapy setting, a 3-hour session might not be as convenient as suggested, as it is not a traditional time frame for a therapy session; it might be difficult to fit into a regular therapist’s schedule and might require too much time and energy at one time for a therapist and a client. It is possible that the same amount of exposure tasks of one session divided into several sessions might be a more logistically comfortable solution in some settings like traditional therapy or outpatient clinics; however, from previous evidence, it is not clear enough how it would affect the VR exposure for public speaking efficacy.

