### Data Collection and Management

#### Plans for Assessment and Collection of Outcomes

Data will be collected at prerandomization, during the sessions, 1 week after the last session before starting the online intervention, after 4 weeks of online intervention, and then at 3- and 12-month follow-ups. Baseline assessment, posttreatment assessment, and follow-up assessments will be completed online. At the beginning of the exposure session, participants will fill in the primary measure again using a paper-and-pencil questionnaire format, and in-session assessments will be filled in the paper session protocol as well. All questionnaires will be based on participants’ self-report. The full timeline of assessments is provided in Table 1.

**Table 1. T1:** Schedule of enrollment, interventions, and assessments for the randomized controlled trial comparing 1-session and 3-session of virtual reality (VR) exposure therapy for public speaking anxiety among young adults.

Assessment/activity	Screening		Postrandomization						Follow-up	
	*t* _−1_ ^a^	*t* _0_ ^b^	*t* _1_ ^c^			*t* _2_ ^d^	*t*_3_-*t*_6_^e^	*t* _7_ ^f^	*f* _1_ ^g^	*f* _2_ ^h^
			Pre-VR exposure	During exposure	Post-VR exposure				3 months	12 months
Informed consent	✓		✓							
Demographic data	✓									
LSAS-SR^i^	✓					✓		✓	✓	✓
PSAS^j^	✓		✓			✓		✓	✓	✓
BFNE^k^	✓					✓		✓	✓	✓
PHQ-9^l^	✓									
IPQ^m^					✓					
In-session assessments: SUDS^n^, catastrophic belief expectancy, quality of performance, single-item presence measure				✓						
Evaluation of intervention format (1-session or 3-session)					✓					
Treatment satisfaction, negative effects								✓		
VR exposure therapy				✓						
4-week online program							✓			
Eligibility criteria	✓	✓								
Treatment expectancy	✓									
Treatment engagement							✓			

a *t*_−1_: online eligibility screening and control data collection (baseline).

b *t*_0_: further screening during telephone interview.

c *t*_1_: face-to-face VR exposure intervention delivery, either via one 3-hour session or via three 1-hour sessions.

d *t*_2_: outcome assessment 1 week after completion of face-to-face VR exposure intervention, either after one 3-hour session or after three 1-hour sessions (first primary endpoint).

e *t*_3_-*t*_6_: 4 weeks of online program with new tasks and materials available weekly.

f *t*_7_: outcome assessment after finishing the 4-week online program or equivalent time if the online program was discontinued (second primary endpoint).

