## Discussion

### The Importance of Different Formats

This study will aim to test whether 1-session VR exposure effectiveness for public speaking anxiety differs from the same amount of exposure tasks divided into 3 sessions over the period of 2 weeks, while both programs include 4 weeks of online intervention after the exposure sessions. We consider this study to address an important and practical question regarding the optimal arrangement of VR exposure therapy delivery for public speaking anxiety. A few previous studies found that one VR exposure session [25,43] and 4 sessions of VR exposure therapy [42] were effective in reducing public speaking anxiety. However, to our knowledge, no previous study directly compared the same exposure tasks performed in 1 session and divided into 3 sessions in the context of VR exposure for public speaking anxiety. One session of exposure therapy might be convenient in some contexts but also might be too intensive and long for traditional therapy settings. Extended VR usage in a short period of time might also introduce additional disadvantages in a 1-session exposure. On the other hand, 1-session exposure therapy might be convenient in some contexts, where the number of possible appointments is limited. In addition, the chances of discontinued treatment are likely to be higher in multiple VR exposure sessions compared to one session. This study will compare exposure tasks divided into 3 shorter sessions and a 1-session VR exposure treatment. The study will test an understudied and clinically important question that could generate preliminary evidence of 1-session versus 3-session VR exposure for public speaking comparison and would have the potential to inform future research into optimizing VR exposure for public speaking. However, given a quite limited and specific sample, results would have to be confirmed in larger and more diverse samples.

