### Limitations

There are several limitations and risks that we anticipate during the trial. First of all, exposure therapy, by the nature of the method, induces anxiety and discomfort. Participants might be more reluctant to participate in the study and drop out after one exposure session. There will be a need to evaluate the discomfort level of the participant and encourage continuation of the exposure even when they experience discomfort; however, in severe cases of negative reactions, exposure will be discontinued. Another problem we anticipate is participants’ reluctance to continue a transition to in vivo exposure during 4 weeks of online intervention. Low compliance was reported in the equivalent program after VR exposure in the previous study by Lindner et al [43]. To increase compliance, we will ask participants to confirm they will be able to participate in the 4-week online program after the exposure by emphasizing the importance and rationale of online intervention during the in-person session. Another limitation is that although we will measure presence and hypothesized that the length of the sessions might be related to cybersickness for some, for a more parsimonious design of the study, other than excluding participants who reported a history of strong motion sickness, we will not explicitly measure and test motion sickness during VR exposure sessions, which could be one of the confounders of the exposure effectiveness between the different conditions. Due to a very specific and convenient sampling strategy in this research, generalization of the obtained results is strictly limited to young adults pursuing higher education and cannot be directly applied to clinical populations or people from other age groups or social categories. Yet another limitation is that this research focuses on the comparison of different delivery methods with the same amount of VR exposure followed by an online program. Since it does not include a control group that does not have an active intervention, this research is not testing whether this VR exposure therapy is more effective than no treatment, treatment as usual, or a stand-alone online program, but explores comparative efficacy.

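### The only solicited negative-effects assessment comes at week 5, after an online program shared by both arms, so it is insensitive to reactions to the VR sessions

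*Protocol article*

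**What the plan says.** Under Other Measures the protocol schedules the harms questions once: "Treatment satisfaction and negative effects will be assessed posttreatment after finishing the online program at week 5". It continues: "Participants will be asked to answer questions about treatment (both VR exposure sessions and online program) satisfaction and report negative effects", and participants also rate the level of these effects. Table 1 has one tick for satisfaction and negative effects, at t7, which its footnote defines as "outcome assessment after finishing the 4-week online program or equivalent time if the online program was discontinued (second primary endpoint". There is no tick in the post-VR column or at t2, which the table describes as "outcome assessment 1 week after completion of face-to-face VR exposure intervention, either after one 3-hour session or after three 1-hour sessions (first primary endpoint".

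The randomised contrast is confined to the VR phase: "Both conditions will be followed by the same 4-week online program to encourage in vivo exposure tasks for both conditions".

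Tolerability of long VR use is part of the rationale. The Introduction refers to "longer VR sessions being associated with increased motion sickness risk", and the Discussion says: "Extended VR usage in a short period of time might also introduce additional disadvantages in a 1-session exposure". Under Limitations the authors disclose that "we will not explicitly measure and test motion sickness during VR exposure sessions".

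**The concern.** The arms differ only in how the VR tasks are spaced, and the protocol itself suggests that a long VR session may be less well tolerated. The one structured question about negative effects comes after four further weeks of an intervention that is identical in both arms. The Limitations section now treats t2 as the main primary endpoint because it follows the phase in which the conditions differ. The same reasoning applies to negative effects, but t2 does not carry them.

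At stake is the reading of a null result. Similar t7 rates could be taken as evidence that the two formats are equally well tolerated, when VR reactions may have been forgotten, lost through non-response, or diluted by effects of the shared program.

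**Working it through.** **Timing.** t2 is 1 week after the last VR session and the online program lasts 4 weeks, so t7 falls 1 + 4 = 5 weeks after the last session. The VR Exposure Sessions section spreads the three sessions over 2 weeks, so in that arm the first may be 5 + 2 = 7 weeks old. At t2 the corresponding gaps are 1 week and up to 1 + 2 = 3 weeks.

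**What else is collected on tolerability.**
- Reasons for discontinuing, with motion sickness as an example (Criteria for Discontinuing). This misses reactions that were unpleasant but tolerated.
- Spontaneous reports of adverse effects, all to be reported (Ethical Considerations). These are unsolicited.
- Weekly therapist reports in supervision (Ethical Considerations). These are not a participant questionnaire.
- Distress ratings before and after each task, including the peak (In-Session Assessments). These measure task distress.
- Ratings of convenience, duration, fatigue, intensity and adaptability at the end of the VR part (Other Outcome Measures). These are solicited and format-specific, but rate the format.

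None of these solicits negative effects such as nausea, or effects in the days after a session.

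**Size of the dilution.** The protocol gives no expected rate of negative effects, so the rates below are assumptions. The arm size is 86/2 = 43, from the Sample Size section. That total reproduces: the G*Power between-factors formula with f = 0.25, three measurements and correlation 0.5 gives power 0.801 at 86. The point does not depend on it. Power is for a two-sided comparison of two proportions at 0.05 (normal approximation).

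Assume true VR reaction rates of 30% and 10%. Asked without loss, the difference is 20 points and power is 0.64.

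*Shared background b from the online program*, observed rate = 1 - (1 - p)(1 - b):
- b = 10%: 1 - 0.70 × 0.90 = 37% and 1 - 0.90 × 0.90 = 19%; difference 18 points, power 0.46.
- b = 30%: 1 - 0.70 × 0.70 = 51% and 1 - 0.90 × 0.70 = 37%; difference 14 points, power 0.26.

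*Share r of reactions recalled at week 5*, observed rate = p × r:
- r = 75%: 22.5% and 7.5%; difference 15 points, power 0.50.
- r = 50%: 15% and 5%; difference 10 points, power 0.34.

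With 40% versus 10%, power starts at 0.91. It falls to 0.77-0.50 under the same backgrounds and to 0.77-0.56 under the same recall loss.

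*Non-response*, assuming 80% of participants without a reaction answer t7:
- 50% of those with a reaction answer: 0.05/(0.05 + 0.72) = 6.5% is seen for a true 10%, and 0.15/(0.15 + 0.56) = 21.1% for a true 30%. The difference is 14.6 points instead of 20.
- 70% answer: 0.07/(0.07 + 0.72) = 8.9% and 0.21/(0.21 + 0.56) = 27.3%; difference 18.4 points.

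Under each of these assumptions the contrast shrinks but does not vanish.

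**The case against.** A reader might infer that the trial cannot attribute negative effects to the 1- or 3-session format at all. The documents do not support that. Format is the only randomised difference and the online program is the same in both arms, so, subject to missing data, a between-arm difference at t7 is an effect of allocated format. What may be lost is the split of events between the VR and online phases, along with sensitivity.

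A reader might also infer that people who stop the online program drop out of t7. They do not: t7 is scheduled at an equivalent time for them, and email and phone reminders are planned for follow-up questionnaires. The low compliance anticipated under Limitations concerns the online program, not questionnaire response. Selective non-response is therefore a possibility, not something the protocol predicts. The Discussion does expect more discontinuation with multiple sessions, so response could differ by arm.

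Three further points stand. The wording of the items is not shown, and the parenthesis covering both components attaches to satisfaction, so the negative-effects items may ask about VR and online separately. That would help attribution, but not recall or non-response. The lack of a motion sickness measure is openly disclosed and is not a separate error. The post-VR ratings of fatigue, intensity and duration are taken without a recall gap and do narrow the problem.

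Finally, the remedy may be late. The article says that the data had already been seen and that publication did not precede the end of the study.

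**Conclusion.** The point holds as a weakness in detecting and locating harms. The only structured, solicited negative-effects assessment comes about 5 weeks after the last VR session and after a shared intervention. The other routes reduce the gap without closing it. A t7 comparison remains a valid comparison of the whole packages, but it is insensitive to VR-session reactions.

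Under the assumed 30% versus 10%, power falls from 0.64 to between 0.46 and 0.26 through background alone, or to between 0.50 and 0.34 through recall loss alone. These figures illustrate direction and rough size. They rest on assumed rates, on 43 per arm, and on complete response except in the non-response example. Only 37 participants had been randomised by November 2025, so a shortfall against 86 would lower power further at the same rates. The primary PSAS analysis is not affected.

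**What to change.** For any participant not yet at t2, add the existing negative-effects items to the online t2 assessment, worded for the VR sessions and placed after the PSAS. Keep the t7 items, and use t2 for the between-arm tolerability comparison. The cost is a slightly longer t2 form and minor rewording.

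For participants already past t2, which may be most or all of them, report by arm over all randomised: VR discontinuations with reasons, recorded adverse effects, and the end-of-VR ratings of fatigue, intensity and duration, showing how many are missing. The protocol already provides for collecting these, so the cost is tabulation.

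In the results report, state that the t7 negative-effects comparison reflects the VR sessions and online program together and is insensitive to VR-session reactions, so that similar t7 rates must not be read as equal tolerability of the two VR formats. If the items do ask about VR and online separately, say so and present them separately.
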